## Methods/design

### Trial design

The Standard Protocol Items: Recommendations for Interventional Trials (SPIRIT) guidelines [33] have strictly been followed in the planning of this trial (Additional file 1).

This trial is a multicenter intention-to-treat randomized controlled superiority trial with parallel arms. Analysis of results will be performed according to the intention-to-treat principle. For the primary objective, only patients are blinded to the allocated intervention (partial or complete caries removal). For the secondary objective (type of adhesive), both patients and investigators are blinded. Outcome examiners and data analysts are always blinded.

Two successive randomizations are performed (allocation ratio 1:1): first, for the type of excavation (P versus C) and second, for the adhesive system (AA) versus TA. The second randomization is not performed for teeth requiring endodontic treatment after the first randomization.

The possible combinations of interventions are in Fig. 1, the flow diagram is mentioned on Table 1 and the flow chart of the study is in Fig. 2.

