**Fig. 1 Fig1:**
[figure not shown]
Combinations of interventions

**Table 1 Tab1:** Flow diagram

	Study period					
	Selection visit	Randomization visit	Postrandomization visit			Emergency visit
Time point	T-1	T0	T0 + 1 yr	T0 + 2 yrs	T0 + 3 yrs	Between T0 and T0 + 3 yrs
Enrolment:						
- eligibility screen	X					
- informed consent	X					
- randomization		X				
Interventions:						
- caries management		X				If needed
- X-ray	X	X	X	X	X	If needed
Control of carious eviction with the SoproLife*®*		X				
assessment:						
- baseline variables	X	X				
- FDI criteria			X	X	X	X
- other data variables listed in the CRF			X	X	X	X

*FDI* FDI World Dental Federation, *CRF* case report form

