### Outcome measures

Cases are considered successful if each of the following five FDI World Dental Federation (FDI) criteria has a final score ≤ 3: material fracture and retention, marginal adaptation, radiographic examination (including apical pathologies), postoperative sensitivity and tooth vitality, and recurrence of carious lesions [48, 49]. A score of 4 or 5 indicates that reintervention is necessary and, therefore, the case is classified as a failure in the context of the study. Criteria are scored at 1, 2, and 3 years’ postintervention by two blinded independent trained evaluators. Study assessing the agreement between evaluators for FDI criteria is ongoing. In cases of emergency visits, FDI criteria will be scored by the investigator.

For the primary objective (P versus C excavation) and the main secondary objective (AA versus TA), the outcome will be the success (yes/no) at 1 year, as defined previously.

For the first secondary objective (identification of factors predicting success at 1 and 3 years), the following candidate factors will be investigated: postoperative pain, patient age, type of carious lesion (primary or secondary), location of the carious lesion, and pulp exposure.

For the second secondary objective (description of the consequences of treatment failure and side effects per treatment arm), the following events will be considered: total number of needed visits, number of endodontic treatments, and number of avulsions.

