### Statistical methods

The statistical unit for analysis will be the tooth. Only one tooth per patient will be included and treated according to the protocol. The demographic and clinical characteristics of patients and treated teeth will be described for both treatment arms with mean and SD or median and interquartile ranges for quantitative variables and number of subjects, and percentages for qualitative variables. The analyses will be performed according to the intention-to-treat principle.

To evaluate the primary objective, the probability of success in arms P and C at 1 year will be calculated and compared by Fisher’s exact test. The probability of success for each arm (0 for treatment failure and 1 for success, at 1 year) will be assessed by a hierarchical logistic model. This model accounts for the correlation related to the hierarchical structure of the data (several patients treated by one practitioner) as well as any possible inter-practitioner heterogeneity. The model will be adjusted on the type of adhesive (arm AA or TA) and on prognostic factors accounted for in the minimization scheme. If necessary, other adjustment factors might also be considered. In cases of patient non-compliance with follow-up visits, the last investigator’s assessment will be used in the analysis, if there is one.

All analyses related to the primary objective (Fisher’s exact test and the modeling approach) will initially include all patients with an available primary outcome as modified ITT. The number of patients to be included has been increased to account for missing outcomes. Then, three sensitivity analyses will be performed: the first according to the maximal bias approach (missing data considered as “success” in arm C and as “failure” in arm P), the second considering all missing data as successes, and the third considering all missing data as failures.

For the secondary objectives comparing efficacy (as defined for the primary objective) at 1, 2, and 3 years and between arm AA and arm TA at the three different times, similar analyses to those used for the primary objective will be performed. The probability of success for each criterion will be assessed and compared between arms by using the hierarchical logistic model described previously.

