All current recommendations (the SPIRIT statement) were taken into account for the design of the present clinical trial [33]. A complete factorial design would have allowed for exploring the interaction between the management strategies (P versus C excavation, and AA versus TA). However, the impossibility of randomizing the adhesive with endodontic treatment, expected to be more frequent with C excavation, led us to adopt a nested design with two distinct and successive randomizations. The tooth was chosen as the statistical unit, with only one tooth per patient, to ensure the independence between statistical units. If a split-mouth design had been chosen, finding patients with two cavities similar in depth would have been difficult. In terms of internal validity, the sources of bias are limited by the use of centralized randomization (selection bias), strict prospective data record and monitoring (information bias), and blinded patients and evaluators (performance and detection bias). However, because of the nature of the investigation, the investigators cannot be blinded.

The choice of assessment criteria is based on the 16 criteria for evaluating direct restorations published and approved by the FDI [48]. As suggested by Hickel et al., a selection of criteria was chosen to match the objectives of the study [49]. The focus was functional properties (material fracture and retention, marginal adaptation, radiographic examination) and biological properties (postoperative pain and tooth vitality, recurrence of carious lesions).

The clinical procedure is carried out under optimal conditions. One of the main points is that partial removal involves only the tissues close to the dental pulp. Indeed, the cavity margins should include no carious tissue so as to avoid the recurrence of the lesion at the tooth-restoration interface. Decay can reach different surfaces of the tooth, but the restoration must be single and unique to avoid any confusion during the evaluation step. For the same reason, the included tooth must be free of cervical carious lesion.

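### The carry-forward rule can turn an early emergency-visit score by an unblinded investigator into a 1-year success that no sensitivity analysis varies

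*Protocol article*

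**What the plan says.** All references are to the protocol article.

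- **Statistical methods** fixes the rule: "In cases of patient non-compliance with follow-up visits, the last investigator’s assessment will be used in the analysis, if there is one". It sets no earliest acceptable date and does not distinguish failures from non-failures. The main analysis "will initially include all patients with an available primary outcome as modified ITT". Three sensitivity analyses follow: maximal bias (missing counted as success in arm C and failure in arm P), all missing as successes, and all missing as failures.
- **Outcome measures** defines the endpoint as success at 1 year, meaning a score of 3 or less on each of five FDI criteria. Scheduled scoring is at 1, 2 and 3 years "postintervention by two blinded independent trained evaluators". Unscheduled scoring is different: "In cases of emergency visits, FDI criteria will be scored by the investigator".
- **Table 1** marks FDI criteria at 1, 2 and 3 years and in the emergency-visit column, which is timed "Between T0 and T0 + 3 yrs". It marks none at selection or at the randomization visit.
- **Trial design** says that for partial versus complete excavation "only patients are blinded to the allocated intervention (partial or complete caries removal", and the **Discussion** confirms that "because of the nature of the investigation, the investigators cannot be blinded". Trial design also says that outcome examiners are blinded in every case, and that investigators are blinded to the type of adhesive.
- **Intervention** makes root canal treatment at the treatment visit a failure for the excavation randomization.

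**The concern.** A failure, once it has occurred, stays a failure for this endpoint, so carrying it forward is sound. A non-failure shows only that the tooth had not failed by that day. Carrying it to 1 year fills an unknown status with a success.

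Three features of this rule add to the problem:

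- **Who scores.** For the primary comparison the carried score comes from someone who knows the arm. The Discussion relies on blinded evaluators as its protection against detection bias.
- **Who gets a score.** Apart from root canal treatment at the treatment visit, a patient who misses year 1 has an outcome only if there was an emergency visit. The article's own hypothesis is that pulp disease is less frequent after partial excavation, so having such a visit could be related to arm.
- **What happens next.** A carried score counts as an available outcome. It enters the modified intention-to-treat set and is beyond the reach of the sensitivity analyses meant to test dependence on unobserved outcomes.

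At stake is a primary comparison in which few failures are expected, and the credibility of the statement that outcome assessment is always blinded.

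**Working it through.** **1. Which outcomes can exist before 1 year.** From Table 1, Outcome measures and Intervention:

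| Source | When | Who determines it | Possible result |
|---|---|---|---|
| Root canal treatment at T0 | Treatment visit | Investigator | Failure only (excavation comparison) |
| Emergency visit | Any time after T0 | Investigator | Failure or non-failure |
| Scheduled FDI scoring | 1 year onwards | Two blinded evaluators | Failure or non-failure |

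The only success that can be carried to 1 year is therefore an emergency-visit score of 3 or less.

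**2. The plan's own sample size.** Inputs from Sample size: 97% v 90% success, two-sided 5%, power above 80%, 10% lost. Exact power of the two-sided Fisher test at 209 per arm is 80.1%, and 418 / (1 − 0.10) = 464.4, which agrees with the stated 464. The sample size is not in question.

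**3. How many patients the rule could touch.** 464 × 0.10 = 46, or 232 × 0.10 = 23.2 per arm. The article does not say what share of these would have an emergency score, so the range 0 to 100% is shown.

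**4. Effect with equal handling in both arms.** Observed per arm: 232 × 0.90 = 208.8. Assume that all carried scores are successes and that observed patients succeed at 97% and 90%. With m carried successes per arm, the analysed rate is (208.8 × p + m) / (208.8 + m).

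| Share of dropouts carried | m | Arm P | Arm C | Difference |
|---|---|---|---|---|
| 0% | 0 | 97.0% | 90.0% | 7.0 points |
| 25% | 5.8 | 97.1% | 90.3% | 6.8 points |
| 50% | 11.6 | 97.2% | 90.5% | 6.6 points |
| 100% | 23.2 | 97.3% | 91.0% | 6.3 points |

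**5. Fisher's test at the planned counts.** Failures: 209 × 0.03 ≈ 6 and 209 × 0.10 ≈ 21, so 6 v 21 of 209 gives p = 0.0045. Adding 6, 12 or 23 carried successes to each arm gives p = 0.0045, 0.0046 and 0.0046.

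**6. Outer bounds if carried scores differed completely by arm** (100% share):

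- All failures in P and all successes in C: 208.8 × 0.97 / 232 = 87.3% v (208.8 × 0.90 + 23.2) / 232 = 91.0%, a difference of −3.7 points.
- All successes in P and all failures in C: 97.3% v 208.8 × 0.90 / 232 = 81.0%, a difference of +16.3 points.

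These are limits, not forecasts.

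**7. What the sensitivity analyses lose.** In the limiting case where all 23.2 per arm carry a success, nothing is left missing, and the maximal-bias analysis returns the main result of 97.3% v 91.0%. If the same patients were treated as missing, it would give 87.3% v 91.0%. At smaller shares the loss is proportionately smaller.

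**The case against.** The strongest reply is that the rule hardly moves the answer. Steps 4 and 5 bear this out when both arms are handled alike, and that part stands. It also stands that the rule applies only where an assessment exists, so dropouts without any score stay missing; that the share with an emergency visit is unknown; and that an unseen analysis plan might set a visit window. The last point does not remove the concern, because the article states a rule and does not leave the matter open.

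Some stronger readings are tempting but unsupported:

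- **That the rule could overturn the primary result.** Moving from 6 v 21 to 10 v 21 failures of 209 does take p to 0.060. But that adds four failures to arm P alone. The mechanism here adds successes, so the example does not describe it.
- **That 3-year success is overstated by a known amount.** Such a figure would need most later dropouts to carry a success. Read literally, the rule carries investigator scores, which come from emergency visits, and not the evaluators' scores at scheduled visits. The article gives no basis for the share.
- **That the adhesive comparison also uses unblinded scores.** Trial design states that investigators are blinded to the adhesive, so only the timing problem applies there.
- **That every early outcome is an emergency score.** Root canal treatment at T0 is an exception, and it is properly a failure for the excavation comparison.

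A last objection concerns the remedy: keeping early failures while setting aside early non-failures makes entry to the modified intention-to-treat set depend on the outcome. This is correct and is dealt with in the fix.

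**Conclusion.** The point holds on the text. As written, an investigator's emergency score of 3 or less, at any time after treatment, becomes a success at 1 year for a patient who then misses that visit. For partial versus complete excavation that score is unblinded, which conflicts with the statement in Trial design that outcome examiners are always blinded; the two statements need reconciling. The planned sensitivity analyses would not vary it.

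The expected size is modest. With 10% loss and equal handling, the difference falls from 7.0 to no less than about 6.3 points, and Fisher's p stays at about 0.0045 to 0.0046. This rests on the planned success rates among observed patients and on all carried scores being successes. A materially larger bias would need scoring or selection that depends on arm, and nothing in the article lets its size be estimated. The rule is worth changing because it is a stated misclassification that the plan has no means of detecting. The article does not show that it threatens the primary conclusion.

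**What to change.** Replace the carry-forward sentence in Statistical methods with a rule of this kind:

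- A score of 4 or 5 recorded by the time point, or an outcome that the protocol already classes as failure for that comparison, counts as failure at that time point.
- An earlier non-failure followed by a missed 1-, 2- or 3-year visit is missing at that time point, and the three planned sensitivity analyses apply to it.

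Amend the blinding statement in Trial design to say that emergency-visit scores are given by investigators who know the excavation arm.

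The change needs no new visits, data or patients. It has two costs. A few more outcomes become missing. And dropouts enter the modified intention-to-treat set only if they failed, which lowers observed success: at the planned counts, one carried failure in arm P takes it from 203/209 = 97.1% to 203/210 = 96.7%. So report the number of carried failures by arm, and show the primary result with and without them.

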### Sample size

According to a literature review [9, 34–42], 97 % and 90 % of success is expected for P and C dentin excavation strategies, respectively. A total of at least 464 patients would be needed for a bilateral test with an alpha risk of 5 % and a power greater than 80 %, supposing at 1 year 10 % of patients lost to follow-up as a ‘not to exceed’ value (calculated by nQuery Advisor 7.0) [43–45].

With the expected recruitment of each investigator, in order to reach the target sample size and respect the inclusion period of 18 months, this trial involves 15 centers. To encourage recruitment, the main investigator sends an encouraging text message after each inclusion and the center recruitment appears on the main page of the randomization website.

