### Randomization

Randomization is performed using a computerized and centralized system via a specific website. A two-stage randomization process allows for integrating the two levels of randomization (i.e., the type of excavation and the nature of the adhesive). A minimization procedure is implemented to take into account the following prognostic characteristics: investigator, patient age (by age group), type of carious lesion (primary or secondary), location of the lesion (proximal or occlusal) and pulp exposure.

Because all patient and cavity characteristics must be entered in the electronic case report form (eCRF) before interventions are assigned, sequence concealment is secured.

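### The primary objective has two analyses, Fisher's exact test and a hierarchical logistic model, and the text does not say which one decides

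*Protocol article*

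**What the plan says.** The Statistical methods section of the protocol article first states that the one-year success probabilities in arms P and C "will be calculated and compared by Fisher’s exact test". It then says that the probability of success in each arm will be assessed by a hierarchical logistic model that allows for clustering by practitioner. That model is adjusted on adhesive arm and on the minimization factors, and further adjustment factors may be added if judged necessary. The next paragraph groups the two ("All analyses related to the primary objective (Fisher’s exact test and the modeling approach") and applies both to all patients with an available primary outcome. The three sensitivity analyses that follow concern missing outcomes only.

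Under Randomization: "A minimization procedure is implemented to take into account the following prognostic characteristics: investigator, patient age (by age group"; the list continues with lesion type, lesion location and pulp exposure.

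Under Sample size: "97 % and 90 % of success is expected for P and C dentin excavation strategies", respectively. The calculation is for a "bilateral test with an alpha risk of 5 % and a power greater than 80" per cent, with "10 % of patients lost to follow-up". The type of test is not named there.

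Three other places bear on the model. Trial design says that teeth needing endodontic treatment are not randomized to an adhesive. Intervention says that a tooth sent to root canal treatment is a failure for the first randomization, and describes pulp exposure occurring after complete excavation. The Discussion expects endodontic treatment more often under C.

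**The concern.** If two analyses of one hypothesis have equal standing, the trial's conclusion can rest on whichever p-value is favourable, or stay open when they conflict. One of the two is also not fully fixed, because covariates may be added later.

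The analyses differ in kind. Fisher's test uses none of the allocation factors and is conservative when success is near 90–97%. The model uses those factors, but it also conditions on variables that are set, or can change, after the first randomization. One of these, adhesive arm, has no value for some teeth that already count as failures. The two analyses can therefore differ in the teeth they include as well as in efficiency.

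**Working it through.** **Inputs.** From Sample size: success 97% (P) and 90% (C), two-sided alpha 5%, power above 80%, 10% loss, total 464. From Trial design: 1:1 allocation.

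**1. Reproducing 464.** Power of the two-sided Fisher test is the sum, over all outcome pairs (x, y), of Bin(x; n, 0.97) × Bin(y; n, 0.90) for pairs with Fisher p ≤ 0.05.
- n = 208 per arm: 79.88%.
- n = 209 per arm: 80.11%, the first of these to exceed 80%.
- 2 × 209 = 418, and 418/0.9 = 464.4, i.e. the stated 464.

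Other standard routes do not give 464. The pooled normal formula gives 194 per arm and 432 after loss. With continuity correction it gives 222 per arm and 494. So 464 is a Fisher design.

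**2. Unadjusted tests at 209 per arm (exact enumeration).**

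| Test | Power, 97% v 90% | Size at common success 90% / 93.5% / 97% |
|---|---|---|
| Fisher | 80.1% | 3.4% / 3.1% / 2.3% |
| Pearson chi-square | 84.7% | 4.9% / 4.7% / 4.9% |
| Likelihood ratio (logistic, arm only) | 85.7% | 5.2% / 5.2% / 6.3% |
| Boschloo exact | 82.3% | maximum 4.96% |

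Fisher and the likelihood-ratio test give different verdicts with probability 5.5% at 97% versus 90%. No outcome pair exists in which Fisher rejects and the likelihood-ratio test does not.

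**3. With baseline adjustment (simulation, 3,000 runs per setting).** Assumptions: four balanced binary covariates, with combined SD of 0, 0.5 or 1 on the logit scale, and no practitioner effect. Fisher's power was 80–82% and the adjusted model's 86–88%. They disagreed in 5.6–7.1% of trials at the design effect, again always with Fisher the non-significant one. The model's size was about 5.6%, so part of its gain is excess type I error.

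**4. The model as written.** Suppose a share f of C teeth goes to root canal treatment, has no adhesive arm and drops out of the model, with none lost in P. All the dropped teeth are failures. Then n_C = 209(1 − f) and p_C = 0.90/(1 − f). With d = 0.97 − p_C, SE₀ the pooled and SE₁ the unpooled standard error, power = Φ[(d − 1.96·SE₀)/SE₁].

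Example, f = 3%: n_C = 202.7, p_C = 0.9278, d = 0.0422, SE₀ = 0.0217, SE₁ = 0.0217. Power = Φ(−0.01) ≈ 50%.

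| f (assumed) | 0 | 1% | 2% | 3% | 4% | 5% |
|---|---|---|---|---|---|---|
| Power | 83% | 74% | 63% | 50% | 35% | 21% |

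Fisher's test keeps these teeth. Under this mechanism it could be significant while the model is not, the reverse of steps 2 and 3. The document gives no value for f, so the table shows sensitivity and is not an estimate.

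**5. Pulp exposure.** Eligibility requires no radiographic continuity between lesion and pulp chamber, and Intervention describes exposure after excavation. Exposure can therefore be a result of the assigned excavation. The Randomization section does not say whether this factor serves only the second stage.

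**The case against.** The strongest reply is that Fisher is plainly meant to decide. It comes first, it is the analysis said to compare the arms, and 464 is its sample size. Later in the same section, where the model is meant to compare arms, the text says so. That makes Fisher the likely intention, so it would be too strong to call the verdict wholly undefined. It remains inference: Sample size names no test, and the grouping sentence gives both analyses the same standing. A separate analysis plan might settle it, but the wording shown here should not leave two candidates.

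A reader might infer that Fisher's conservatism leaves the trial underpowered. It does not. The calculation already pays for it (464 against 432 by the pooled normal formula), and the target of "a power greater than 80" per cent is met. Power is lower only relative to other tests.

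A reader might also infer that adjustment buys power at no cost. The likelihood-ratio test reaches 6.3% size at 97% success, and the simulated adjusted model ran at about 5.6%. Only about 27 failures are expected (209 × 0.03 ≈ 6 and 209 × 0.10 ≈ 21), so preferring an exact test is defensible.

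It can also be said that choosing between two p-values does little harm. For the unadjusted pair that is largely right: the tests are nested, so the chance that either rejects under the null is the likelihood-ratio test's own 5.2–6.3%. The argument fails for the model as written, which may analyse different teeth and has an open covariate list.

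Finally, the fall to 21% power should not be read as a prediction. It needs 5% of C teeth, half of that arm's expected failures, to drop out with none from P.

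**Conclusion.** The point holds as a specification defect that is cheap to repair. The protocol gives two analyses of the primary objective, ranks neither and has no rule for disagreement. For the unadjusted pair, disagreement at the design effect is 5.5% and runs one way. For the model as written it could run the other way, because adhesive arm is undefined for teeth that count as failures and are expected mainly in C. The size of that second effect is unknown.

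The exact figures assume 209 evaluable teeth per arm, the protocol's success rates and independent binomial outcomes. The adjusted-model figures rest on assumed covariates and leave out the practitioner effect. The documents do not support a claim that the stated power is missed or that Fisher's test is an error.

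**What to change.** Name one deciding analysis of P versus C before the data are unblinded, and label the other supportive. Either choice works:

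- **(a)** Keep an unadjusted exact test as decider, consistent with 464, with the model supportive. Boschloo's test is preferable to Fisher's: power 82.3% against 80.1%, with maximum size 4.96%.
- **(b)** Make the decider a logistic model with an investigator effect, adjusted only for age group, lesion type and lesion location, with the exact test supportive. Fix the test statistic and a non-convergence fallback in advance, because likelihood-ratio size can exceed 5%.

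Under either choice, remove adhesive arm, post-randomization pulp exposure and the optional extra covariates from the P versus C model, so that every tooth with an outcome is included.

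The cost is analysis-plan wording. Option (b) also needs the fallback rule and may carry slight size inflation. Its power with the investigator effect has not been checked here and should be before it is adopted. Option (a) needs no new sample size work.

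### At the planned effect and the 10% loss ceiling, the maximal-bias analysis is a foregone negative, the all-success analysis nearly repeats the main one, and no intermediate missing-data assumption is named

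*Protocol article*

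**What the plan says.** The Statistical methods section of the protocol article says that the primary analyses, Fisher's exact test and a hierarchical logistic model, "will initially include all patients with an available primary outcome as modified ITT". It then states that "three sensitivity analyses will be performed: the first according to the maximal bias approach". Maximal bias means that missing outcomes count as successes in C and failures in P. The second analysis counts all missing outcomes as successes, the third all as failures. If a follow-up visit is missed, the last investigator assessment is used where one exists.

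The Sample size section supplies the design figures:
- The effect: "97 % and 90 % of success is expected for P and C dentin excavation strategies, respectively".
- The size: a minimum total of 464, for a two-sided 5% test with more than 80% power.
- The allowance for attrition: "supposing at 1 year 10 % of patients lost to follow-up as a ‘not to exceed’ value".

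Three other places bear on who has an outcome. Under Intervention, root canal treatment at the treatment visit (T0) is a failure for the excavation comparison. The Discussion expects endodontic treatment to be more frequent after complete excavation. Table 1 and Outcome measures place FDI scoring at the yearly visits and at emergency visits.

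**The concern.** Sensitivity analyses should show whether the conclusion survives departures from the main missing-data assumption that could really occur. All three stated analyses are single-value extremes: within an arm, every missing tooth succeeds or every one fails. The planned effect is 7 points and the loss allowed for is 10%, so a rule that sets all missing teeth against P can outweigh the whole effect. If one analysis fails almost whatever the data show, another barely moves, and the third loses significance, the reader cannot tell which to believe.

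There is a second, smaller issue. A T0 root canal failure is known without any follow-up, while every other outcome needs a 1-year or emergency visit. Availability therefore depends partly on outcome, and more so in the arm with more T0 failures. That would tilt the main analysis towards P, the arm the trial hopes to support.

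**Working it through.** **Inputs.** Success 0.97 (P) and 0.90 (C), total 464, two-sided 5%, loss 10% (Sample size); allocation 1:1 (Trial design), so 232 per arm; Fisher's exact test (Statistical methods).

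**The plan's own figure.** Exact Fisher power is 80.1% with 209 per arm (79.9% with 208). Then 2 × 209 / 0.9 = 464.4, against 464 stated, so the sample size is reproduced. Loss of 23 per arm (23/232 = 9.9%) leaves 209 observed.

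**Expected differences, with equal loss d in both arms.**
- Maximal bias: 0.97(1−d) − [0.90(1−d) + d] = 0.07 − 1.07d. This is zero at d = 0.07/1.07 = 6.5%. At d = 0.10, P is 87.3%, C is 81.0% + 10% = 91.0%, and the difference is −3.7 points.
- All-success and all-failure: 0.07(1−d), or +6.3 points at d = 0.10 (97.3% v 91.0%, and 87.3% v 81.0%).

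**Whole-number tables at 23 missing per arm**, with observed successes 203/209 (P) and 188/209 (C):

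| Analysis | P | C | Fisher p | Power for P |
|---|---|---|---|---|
| Available outcomes | 203/209 | 188/209 | 0.0045 | 80.1% |
| Maximal bias | 203/232 | 211/232 | 0.29 | about 0% |
| All-success | 226/232 | 211/232 | 0.0046 | 80.1% |
| All-failure | 203/232 | 188/232 | 0.074 | 35.7% |

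The power column assumes that missingness is unrelated to outcome. On the same basis, maximal bias gives a point estimate favouring C in 94% of trials and a significant result for C in 14%. Even if all 209 observed P teeth succeeded, it would give 209/232 (90.1%) v 211/232 (90.9%).

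**Maximal bias at lower loss, planned rates.**
- 4 missing per arm (1.7%): p = 0.049.
- 5 per arm (2.2%): p = 0.078.
- 12 per arm (5.2%): 213/232 v 210/232, p = 0.74.

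**Unequal loss, total about the same.**
- P 28, C 18 missing: all-failure +2.2 points (p = 0.61).
- P 18, C 28: all-failure +10.3 points (p = 0.003).
- P 35, C 12: all-failure −3.0 points.
- All-success stays between +5.6 and +6.9 points in scenarios of this kind.

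**Outcome-dependent availability.** Let f be the true failure rate, r the part of it occurring at T0, and l the loss among the remaining teeth. The failure rate among available teeth is [r + (f−r)(1−l)] / [r + (1−r)(1−l)]. The protocol gives no T0 failure rates, so r is assumed to be 3–8% in C and 0–1% in P. At l = 0.10:
- C, r = 0.08: 0.098/0.908 = 10.79%. C, r = 0.03: 0.093/0.903 = 10.30%.
- P, r = 0: 3.00%. P, r = 0.01: 0.028/0.901 = 3.11%.
- Difference: from 10.30 − 3.11 = 7.2 to 10.79 − 3.00 = 7.8 points, against a true 7.0. The excess is 0.2 to 0.8 points.

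Under the same assumptions all-success gives 6.5 to 7.1 points and all-failure 6.3.

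**The case against.** The strongest reply is that maximal bias is openly labelled a worst case. A bound need not be plausible, and failing at high loss is what bounds do. The 10% is a ceiling, and the last-assessment rule and the retention payment should lower actual loss. At up to 4 missing per arm the bound still confirms the result. The article is condensed and the analysis plan is not shown, so the lack of further methods cannot be held against it.

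Most of this stands, and it limits the point. The absence of multiple imputation from an article is not in itself a defect. But the article fixes and defines its three analyses, and how they behave at its own design figures can be judged. Staying under the ceiling does not rescue maximal bias: at about half of it, p is already 0.74.

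A reader might go further on four counts, and the documents do not support it.
- **That none of the three analyses can inform, or that two agree by construction.** The 10% shrinkage applies to the risk difference under equal loss. All-failure also adds variance, moves p from 0.0045 to 0.074, and responds strongly to unequal loss.
- **That maximal bias would overturn a successful trial.** Only the point estimate changes sign. A significant result for C has a 14% chance.
- **That success requires the 1-year visit.** An emergency assessment with every criterion at 3 or below can be carried forward as a success.
- **That the tilt towards P goes unchecked.** Under the assumed rates, all-success and all-failure overstate the true difference by at most 0.1 point.

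**Conclusion.** The point holds in a limited form. At 97% v 90% and balanced 10% loss, maximal bias is decided before the data arrive, all-success adds almost nothing, and all-failure is the one analysis of the three that can discriminate. A trial performing as designed would report p = 0.0045 in the main analysis and non-significant results in two of three sensitivity analyses, with nothing in between to help interpret the conflict. The tilt of the available-outcome set is modest, and its size rests wholly on assumed T0 failure rates. Only its direction follows from the protocol.

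The figures assume 232 per arm, equal loss unless stated, and missingness unrelated to outcome for the power values. If actual loss is about 1 to 2%, maximal bias can still confirm the result and the problem largely disappears. This is a worthwhile, inexpensive improvement and not a flaw that invalidates the plan.

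**What to change.** Add to the Statistical methods section, or to the analysis plan by cross-reference:

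1. **Multiple imputation of the 1-year outcome, separately by arm.** Use the minimization factors known before the first randomization (investigator, age group, primary or secondary lesion, location), plus what happened to the tooth at T0 and at any emergency visit. T0 root canal failures already have an outcome. The model must condition on that status, so that their failure rate is not passed on to teeth lost later. At the planned rates only about 6 observed failures are expected in P (209 − 203), so the model needs few terms or penalisation.
2. **A tipping-point analysis.** Raise the failure odds of missing P teeth step by step and report where the conclusion changes, so that readers can judge whether that point is credible.
3. **Keep the stated analyses.** Maximal bias becomes the extreme end of that curve, reported alongside all-success and all-failure.

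The cost is a few hours of analysis work and some wording, with no new data or change to the trial's conduct. If the unseen analysis plan already contains this, one sentence of cross-reference is enough.
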